**Visit Procedures:**

1. We will consent women to participate in this ancillary study using an additional procedures consent form.
2. Women will complete one interview, either in a face-to-face or ACASI format. Women will be randomized to one of these interview modes.
3. Women will provide a self-collected vaginal swab for PSA testing. The swab will be self-collected using procedures developed for the MIRA trial.
4. The vaginal swabs will be air-dried and shipped in batches to the University of North Carolina, Chapel Hill for PSA testing in [name]’s laboratory.

**Perceived or potential repercussions of sub-study procedures/objectives on the main trial:**

Although we acknowledge that this ancillary study will require site staff to perform additional procedures (outlined above), the overall burden is relatively small compared to the importance of the additional study question addressed. Staff (e.g., site coordinator, interviewers and outreach workers) will be designated as responsible for recruitment, overseeing PSA study implementation, and ensuring timely storage and shipment of all specimens. MIRA Study coordinators and investigators will discuss the appropriate staffing requirements for this study.

**Data management & analysis plan:** To make this ancillary study less of a burden for the site, the short FTF data collection forms (DCFs) will be shipped to Family Health International (FHI) for data entry. Copies of the DCFs will remain at the site should data queries need to be resolved. The ACASI data will be accumulated by UCSF’s data management group (CIDEA). Data from the three data sources (PSA lab values, ACASI data and FTF data) will be merged into one data set at FHI for analysis. All key investigators listed below will be involved in the analysis and will have written sign-off on manuscripts/presentations.

**Estimated costs:** The primary costs are PSA testing, staffing for study implementation, and the materials involved in collecting and shipping specimens and in printing the short FTF paper interview. Other site costs may include local transport and lab technician time to package specimens for storage and shipment. We have developed a budget jointly that reflects anticipated costs.

**Funding source(s):** FHI/CDC

**Monitoring plan:** Not applicable; a local staff will be assigned primary responsibility for the oversight of this ancillary study. All data queries will be managed by this assigned staff person.

**BACKGROUND**

Research into cervical and chemical barriers to HIV/STIs such as the diaphragm and vaginal microbicides is underway to expand options for disease prevention. If proven effective, these female-controlled methods will be particularly useful for women in settings where male condom use is difficult because of structural-level or relationship-level factors such as culture, gender dynamics, socio-economic circumstances or relationship power. It is important to understand the role of the male partner in influencing women’s acceptability and use of these disease control methods.

**RESEARCH PROTOCOL**

**Study Aims**

The overall goal of this study is to measure and describe the effect of male involvement on women’s adherence to (i.e. uptake of) male condoms[[6]](#footnote-4) and female-controlled methods of HIV/ STI prevention. “Male involvement” encompasses the actions, preferences and attitudes of the primary male partner. The objectives of the study are below. In the data analysis section of this document there is a more in-depth description of how each aim will be addressed analytically.

**Primary aims**

1. To measure quantitatively and describe qualitatively the effect of male involvement on women’s adherence to the diaphragm, gel and male condoms.
2. To measure quantitatively and describe qualitatively the effect of male involvement on acceptability of the diaphragm, gel and male condoms.

**Secondary aims**

1. To examine whether a small intervention promoting male involvement through invitation letters and male ID cards makes an impact on a) level of male involvement; b) women’s adherence and acceptability.
2. To examine correlates of “high” vs. “low” involvement of male partners, using female and male demographic, behavioural, clinical and attitudinal data.
3. To measure whether there is an association between male involvement and STI/ HIV incidence.
4. To measure whether there is a change in different components of male involvement over time.

**METHODS**

The methods section of this document will outline the study design, data collection methods and analysis plan, including sample size considerations.

**Study Design**

All women in the MIRA study are eligible for the Male Involvement Study. Men are invited to come to the study clinics for information and/or HIV/STI counselling and testing. Early experience in MIRA showed that despite this tacit invitation, the promotion of male involvement was ineffective. As a result, a minor intervention component was added to MIRA, which includes offering every enrolled female participant an invitation letter and/or a doctor’s letter and/or a study ID card for the male partner.

The Male Involvement Study began in December 2004 with the introduction of the Male Partner Involvement Form, administered to all women enrolled in the MIRA study. Data collection will continue through September 2006. Focus group and in-depth interview data will be collected from July 2006 through March 2007.

**Data collection methods and activities**

***Data source 1: The Male Partner Involvement Form (MPIF)***

The major source of “male involvement” variables that will be used for exploring the domain of “male involvement”, and correlating male involvement with adherence, acceptability and other demographic, behavioural and clinical data are from the Male Partner Involvement Form.

This questionnaire is administered to female study participants of the Zimbabwe MIRA site (n=2500) at Months 3 and 12. The form has 58 questions. Approximately half of the responses have dichotomous yes/no responses, and the other half have continuous scales. Five items have specify lines for greater open-ended detail, e.g. “Have you invited him to come for free HIV and STI testing? If no why not (specify)________________”.

The aim of the questionnaire is to measure women’s perception of the quantity and quality of her partner’s involvement in study participation and study product use. The form attempts to explore the domains of partner communication, participation and control, and male partner’s attitudes and support for condom, diaphragm and gel use. Questionnaire items were constructed from a variety of sources, including the parent study instruments, previous qualitative studies done in Zimbabwe and other parts of southern Africa, and anecdotal discussions during pilot testing with male Zimbabwean research staff.79-84

The Male Partner Involvement Form was translated and back-translated into Shona from the English, and is interviewer-administered by female (to match respondents) study staff in either language, although the vast majority are in Shona (~99%). Interviewers hold tertiary-level degrees, and have a minimum of 3 years of interviewing experience. Interviewers receive extensive protocol training, form-specific training, and sign-off on SOPs which outline the intention item-by-item, of each question on each form in the study. Data will be double-entered into an Access database, and exported into SAS for analysis.

Table 1 below summarizes the anticipated sample size and the data collection points for this portion of the study, accounting for women who had already passed the first and second data collection points for the Male Involvement Study at the time of implementation.

***Table 1. Expected sample size for Male Partner Involvement Form, by study and data collection time point, (December 2004 – September 2006)***

| *Study* | **Data collection time points** | | | |
| --- | --- | --- | --- | --- |
| **Month 3** | **Month 6** | **Month 12** | **Total sample** |
| *MIRA** | 1160 | NA | 2237 | **3397** |
| ***TOTAL SAMPLE*** | ***1160*** | ***116*** | ***2237*** | ***3602*** |

*Form administered after start of MIRA study, therefore approx. half of the participants had already passed the Month 3 visit, and only 15 had completed the Month 12 visits. Form administered at next subsequent visit if scheduled visit missed. Estimates include 10% projected loss-to-follow-up.

**Male Questionnaire**

Originally a self-administered questionnaire to male partners of female study participants was considered. This methodology was not adopted.

***Data source 2: Existing data about male partners and female product adherence and acceptability***

In addition to the new data specifically being collected for the Male Involvement Study, data are being collected on male partners through Audio Computer-Assisted Self-Interview (ACASI) interviews and on Case Record Forms (CRFs) as part of the main clinical trial. For example, partner’s age, employment, migration, marital status, multiple partnerships, use of alcohol/drugs and violent behaviour. Questions also cover some aspects of product use disclosure and clandestine use, relationship control and decision-making. Questions about product acceptability contain partner factors in the list of potential responses women can choose.

The primary outcomes of the Male Involvement Study - women’s adherence and acceptability - will be measured from data collected in the main study, as will the HIV/STI incidence data for the secondary objective analysis. Study product adherence is notoriously difficult to measure, as it relies on self-report and is subject to several potential sources of bias, most notably social desirability and recall bias. In an attempt to minimize the former, the MIRA study uses ACASI interviews, mentioned above, which seek to encourage greater honesty (and minimize data processing error) by direct entry of potentially sensitive responses into a computer. To address the latter challenge of recall bias, participants are asked about use of each study product for three different time periods: last act of sex, sex in the past week, and sex in the past three months. Although these time periods all have strengths and limitations, triaging recall periods should contribute to an understanding of the reliability and validity of the measures.

***Data source 3: Focus group discussions (FGDs) with women and men***

The focus groups are intended to complement the quantitative analysis by describing the effect of male involvement on women’s adherence and acceptability of products. The focus groups will also capture male perspectives not in the quantitative data.

A total of 12 focus group discussions, comprising 6–12 members each, will be conducted: four with male partners of MIRA diaphragm-arm participants, and eight with female study participants (4 per arm). The main aim of these FGDs will be on diaphragm, gel and condom acceptability, feasibility and use, exploring the related issues of relationship dynamics, partner communication, contraceptive use, covert use of products, affordability and access of products.

These focus groups are part of the social science component of the MIRA trial and were not specifically designed for the Male Involvement Study. However, [name] had substantial substantive input into the composition of the focus group guides, and is the “Principal Investigator” and will lead the analysis for the “male partners” theme group.

Sample selection - FGDs

At the final MIRA study visit, women are asked to give permission 1) to be contacted for future research related to MIRA and 2) for staff to contact their partner to participate in discussions with other men. Two waves of focus group discussions will be held with participants who have recently exited the trial. The total number who have agreed to be contacted and closed out in the past 3 months, will then be divided by the number of slots available in group discussions, such that every –nth participant will be contacted. This process will be fully documented, and the number of acceptances/refusals will be logged. FGDs will be attended by trained facilitators and note-takers, will be conducted in the local language (Shona), and will follow guides that are available in Appendix D&E. FGDs will be tape-recorded, transcribed and translated into English. Transcripts will be uploaded into Atlas.ti for coding and analysis. Thematic coding will be based on a structured coding dictionary, and will be performed by more than one person to ensure inter-coder reliability. Discrepancies will be settled by panel discussion.

***Data source 4: In-depth interviews (IDIs)***

Approximately 12-20 IDIs will be conducted with men and women to further explore the meaning of partner involvement and its impact on acceptability and adherence to study products. While focus groups are useful for gathering data on community norms, in-depth interviews should more specifically elucidate individual circumstances around the influence of male involvement and the outcomes of interest. To encourage open communication, male and female partners will be interviewed separately. IDIs will follow a semi-structured interview guide, but will allow for iteration and flexibility to probe on issues raised by the respondents. The IDI guides are not yet developed.

Sample selection - IDIs

As above, only participants who have agreed to be contacted will be considered for selection. Couples will be purposively sampled based on the degree of male involvement: Ideally a minimum of 2 with high indicators of involvement, 2 with low indicators, and 2 middle-level. Within each purposive strata, couples will be selected at random using a random number generator program. For example, if 500 women are categorized as having “highly involved” partners, the program will select 2 numbers, and the corresponding ID numbers will be contacted. In qualitative research there are no set formulas to determine an appropriate sample size. 12-20 should offer enough breadth of representation to responses, while not saturating the data. This is a commonly used approach in qualitative research, and requires that the data is reviewed in real-time as it is being collected, so that the Investigator can identify the point at which new data is no longer adding information about the research question to the existing body of data.85

The process for documenting sample selection, as well as transcribing, translating, coding and analyzing data will be equivalent to that done with the focus groups.

***Data source 5: Service Statistics***

As previously mentioned, men are told they are welcome to come for free HIV/ STI counselling and testing to the MIRA study, but this is only happening to a small degree (~1-3% of partners coming). From April 2006, invitation letters and doctor’s notes to excuse men from work were offered to women to give to their male partners. Documentation of services accessed during the study can be tabulated. Several analyses can then follow, for example “came to the clinic = y/n” can be created as a male involvement variable that is fed into an outcome-based model of women’s adherence. Characteristics of women whose partners came vs. did not will be analyzed.

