***Secondary Study Aim 1: Impact of more active male promotion on a) level of male involvement and b) women’s adherence and acceptability of products***

This component of the analysis will evaluate the success of intervention efforts to promote male involvement in the research studies through invitation letters and study ID cards for men. The intervention uptake rate will be tabulated, including a breakdown of whether men came to the clinic, accessed counselling and/or testing for STIs and/or HIV. In the qualitative portion, the study will explore reasons for coming/not coming, and what would have encouraged him, etc. A comparison of characteristics of women whose partners came/did not come will be conducted through bivariate and multivariate analyses. Secondly, this analysis will aim to address whether men coming to the research clinic, as encouraged, had a significant effect on women’s product usage or acceptability, in other words, to evaluate the effect of the intervention.

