***Secondary Study Aim 4: Measure whether there is a change in different components of male involvement over time.***

The Male Partner Involvement Form will be administered at 2 time points to the majority of women. It will thus be possible to examine changes in reported male involvement over time, and correlate this with trends in product adherence and acceptability. For women whose partners come to the clinic between the time points of the questionnaire administration, it will also be possible to measure an “intervention effect”. The qualitative research will also offer insight into potential changes in both male involvement and the outcomes of interest (adherence and acceptability) over time.

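### As planned, the Male Involvement Study does not identify the effect of its letter and ID-card intervention: the offer goes to every woman, and the analysis compares couples by whether the partner came to the clinic

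*Protocol*

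**What the plan says.** All references are to protocol Appendix 16.7 (Male Partner Involvement Study) unless stated.

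- **Aim.** The first secondary aim is to see whether a small intervention, invitation letters and male ID cards, changes (a) the level of male involvement and (b) women's adherence and acceptability.
- **Who is offered it.** Study Design says every enrolled woman is offered an invitation letter, a doctor's letter and/or an ID card for her partner. It gives no date.
- **When.** Data source 5 dates part of the package: "From April 2006, invitation letters and doctor’s notes to excuse men from work were offered to women". The ID cards have no stated start date. The same section says about 1-3% of partners were coming under the earlier open invitation.
- **The form.** "The Male Involvement Study began in December 2004 with the introduction of the Male Partner Involvement Form". Its schedule: "This questionnaire is administered to female study participants of the Zimbabwe MIRA site (n=2500) at Months 3 and 12". For its end: "Data collection will continue through September 2006".
- **Planned analysis.** Secondary Study Aim 1 tabulates uptake, compares women whose partners came with those whose partners did not, and asks whether men's coming changed women's use or acceptability, "in other words, to evaluate the effect of the intervention".
- **Claim under Secondary Study Aim 4.** "For women whose partners come to the clinic between the time points of the questionnaire administration", the plan says an intervention effect can also be measured.

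**The concern.** The intervention is an offer, but the exposure analysed is the partner's response to it. A man who comes to a research clinic is likely to differ beforehand from one who does not, in communication, support and attitude to the products. Those are the traits the study expects to drive adherence. A difference between attenders and non-attenders would be expected even if the letters did nothing.

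Nothing in the plan restricts attendance to visits made after a letter was offered. A man who came under the earlier open invitation would count towards the effect of an intervention he had not received.

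At stake is a false attribution. The appendix describes greater male involvement as a cheap, low-technology approach with public-health potential. A positive attendance contrast reported under the present wording would credit the letters with differences between couples that were already there.

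**Working it through.** **Step 1. Aim against contrast (no arithmetic).**

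| | What the appendix says |
|---|---|
| Question | Do letters and ID cards change involvement and adherence? |
| Exposure offered to | Every enrolled woman |
| Contrast analysed | Partner came / did not come |
| Attendance without letters | About 1-3% |

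With no unexposed group, the effect of the offer could come only from comparing periods before and after it. No such comparison is planned.

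**Step 2. Reproduce the plan's figure.** Inputs: 2,500 women, 10% loss and 13 missing women (power section for adherence). 2,500 × 0.90 − 13 = 2,237, which matches the expected Month 12 forms exactly.

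**Step 3. Infer the timeline.** The appendix's Table 1 expects 1,160 Month 3 forms after loss.

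- Women reaching Month 3 after December 2004: 1,160 / 0.9 = 1,289, so enrolled after about September 2004.
- Women enrolled before that: 2,500 − 1,289 = 1,211, or 48%. This agrees with the table note that about half had passed Month 3.
- If all 2,237 Month 12 forms are in by September 2006, enrolment ended by about September 2005, and the last scheduled Month 3 form falls in about December 2005.
- A scheduled Month 12 form after the start of April 2006 requires enrolment after the start of April 2005.

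**Step 4. Share of Month 12 forms after the letters.** Assume even accrual from September 2004. The 15 women already past Month 12 are removed, leaving 2,485.

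Base case, enrolment ending September 2005 (13 months of accrual, 7 of them before April 2005):

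- Month 12 before April 2006: 1,211 + (7/13) × 1,289 − 15 = 1,890, and 1,890 / 2,485 = 76%.
- Month 12 after: (2,485 − 1,890) × 0.9 ≈ 535 forms, or 24%.

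| Assumed end of enrolment | Month 12 before April 2006 | Forms after | Share after |
|---|---|---|---|
| May 2005 | 88% | about 258 | 12% |
| September 2005 | 76% | about 535 | 24% |
| November 2005 | 72% | about 619 | 28% |

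The last row goes beyond what Table 1 and the September 2006 end of collection allow. It is kept as an outer bound because Appendix 16.6 places all scheduled closing visits before December 2006.

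**Step 5. Other denominator.** Only women with a Month 3 form can contribute to a two-form comparison. Against 1,160, the women with forms on both sides of April 2006 are 535 / 1,160 = 46% (258 / 1,160 = 22% to 619 / 1,160 = 53%). Even for them, the forms are nine months apart. With a Month 12 form by September 2006, at most about six of those months follow the letters, so a visit between forms may still predate any letter.

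**Step 6. Can existing data support a before-after comparison?** Product use is recorded at every quarterly visit (Section 8.5), and Data source 2 takes adherence from the main study. Take 15 women enrolled by December 2003 and even accrual of the other 1,196 (1,211 − 15) over the nine months to September 2004. Then 15 + (1,196 / 9) × 4 ≈ 547 women had passed 24 months by April 2006. That leaves up to 2,500 − 547 ≈ 1,953 who could still be in follow-up, ignoring losses.

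**The case against.** **Form timing does not govern the whole aim.** Adherence comes from quarterly main-trial data and attendance from service statistics, so neither depends on the two form dates. This stands. A reader might infer that the study cannot measure the letters' effect at all; the documents do not support that. Data on both sides of April 2006 exist, and the fault is that the plan does not use them that way. Form timing does matter for part (a) of the aim, since Data source 1 makes the form the main source of involvement variables.

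**Aim 4 is conditional.** It speaks only of women whose partners came between the two forms, not of all Month 3 to Month 12 change. This is correct. But the condition is itself self-selected attendance, and calling the result an intervention effect repeats the fault.

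**The dates are inferred.** A reader might infer that every Month 3 form predates the letters. That holds only for scheduled forms under a back-derived enrolment end. A missed form is given at the next visit, and Section 9.9 accepts a quarterly visit up to 5.5 months late, so a Month 3 form due in December 2005 could be completed in about May 2006. April 2006 also dates only the letters and doctor's notes.

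**The number of informative couples is unknown.** Applying 1-3% to 535 women gives 5 to 16 attending partners and suggests the comparison is hopeless. That rate predates the letters, which were meant to raise it, so the count should not be relied on.

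**Confounding is acknowledged.** Multivariate analyses are planned, and the limitations section mentions selection bias and uncontrolled confounders. Adjusting for measured characteristics does not turn a partner's choice into the effect of an offer, and the limitations are not tied to this contrast.

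**Conclusion.** The point holds in a limited form. The attendance contrast in Secondary Study Aim 1 does not estimate the effect of offering letters or ID cards, and the between-forms claim in Secondary Study Aim 4 has the same defect. This follows from the text alone, without any accrual assumption, and applies equally to the ID cards.

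The timing adds to it. The two-form comparison can bear on the letters for about a quarter of expected Month 12 forms (range about 12-28%), or about 46% of women with both forms (22-53%). These shares assume even accrual after September 2004, scheduled visit dates and an inferred enrolment end.

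A reader might go further and infer that any positive result would be false. It would be a real association wrongly labelled as an effect. The matter is confined to a secondary aim of a sub-study, but it should be corrected because the analysis as worded answers a different question from the one asked.

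**What to change.** 1. In Secondary Study Aims 1 and 4, report partner attendance against adherence, acceptability or involvement as an association only, and remove the wording about evaluating the intervention or measuring an intervention effect.
2. For Secondary Study Aim 1, compare partner-attendance counts and women's quarterly ACASI adherence before and after the date of offer, adjusting for time since enrolment and calendar trend. Use April 2006 for the letters and doctor's notes.
3. State when the ID cards began, and analyse them from that date.
4. Label the result an uncontrolled before-after comparison.

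The cost is sub-study wording and a modest extra analysis; the attendance records and quarterly adherence data are already collected. The weakness that remains is real: the letters began for everyone at about the same time, so separating their effect from a calendar trend rests on the model, and the comparison can still reflect time trends.
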